### Randomizing and blinding

2.5

The randomization will be performed using a random number table that is generated by the statistical program SAS Version 9.4 (SAS Institute Inc, Cary, NC) and is kept secret by the statisticians who are independent of this study. This trial is open-label, but assessors and analysts are blind to allocation and the intervention clinicians will not involve in any assessment.

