### Study design

2.2

The flow chart of the selection of patients is shown in Figure 1. In the current trial, 100 eligible patients with PHH will be recruited from the Department of outpatient of Sichuan University West China Hospital since September 1, 2020, and randomly assigned to the ELD group (study group) and non-ELD group (control group). Lumbar puncture (LP) will be performed for participants in non-ELD group. LP plus ELD will be performed for participants in ELD group, those who will then be investigated the suitability of potential LPS 4 days after ELD. Two independent and practiced assessors will collect the baseline data and evaluate each participant 4 days after ELD or LP, 1 day after LPS, at the time of discharge and 1 month after LPS. The primary outcome is the shunting outcomes 1 month after surgery. The secondary outcomes include the complications related to ELD, complications related to LPS, and Evens index at each evaluation point. Meanwhile, serious adverse events occurring at any time is recorded to determine the safety of this trial.

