### Temporary ELD

2.7

ELD is performed under local infiltration anesthesia and the patients are positioned in the left lateral position. A lumbar catheter is inserted through the L3/4 or L2/3 interlaminar space into the spinal subarachnoid space and then connected to the drainage system. According to previous studies, the drainage period is 3 days and drainage volume is 150 to 200 mL per 24 hours.^[8]^

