### Preoperative evaluation

2.8

Repeated evaluation will be performed using the scale, as shown in Table 1, 4 days after ELD to investigate the suitability of potential LPS and then the ELD system will be removed. Patients with scores 4 will be included in this trial and the remaining patients will be excluded. Specifically, the improvement of clinical manifestation is defined as an improvement of 1 point or more in the National Institute of Health stroke scale, Glasgow coma scale, modified Rankin scale, or according to self-assessment.

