### Outcomes

2.9

Two independent and practiced assessors will collect the baseline characteristics and evaluate each participant 4 days after ELD or LP, 1 day after LPS, at the time of discharge and 1 month after LPS. The evaluation schedule is shown in Table 2.

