#### Primary outcome

2.9.1

The primary outcome is the shunting outcomes 1 month after surgery. Shunting outcomes include shunt failure and shunt success. According to previous studies, which is defined as the shunt obstruction, breakage, tubing exposure, malfunction, or infection requiring shunt revision. Shunt success is defined as the absence of shunt failure.

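### The schedule reveals the allocation to the assessors on day 4, before the same two people evaluate the 1-month primary outcome, so the stated assessor blinding does not hold as written

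*Protocol article*

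**What the plan says.** Section 2.5 (Randomizing and blinding) makes the claim: "This trial is open-label, but assessors and analysts are blind to allocation and the intervention clinicians will not involve in any assessment".

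Section 2.9 (Outcomes), repeating section 2.2, has two assessors collect baseline data and then "evaluate each participant 4 days after ELD or LP, 1 day after LPS, at the time of discharge and 1 month after LPS". Section 2.10 (Data collection) gives data collection to two assessors described in the same terms. Section 2.9.2 lists ELD complications among the secondary outcomes.

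On the procedures, section 2.7 (Temporary ELD) says: "A lumbar catheter is inserted through the L3/4 or L2/3 interlaminar space into the spinal subarachnoid space and then connected to the drainage system". For controls, section 2.2 says: "Lumbar puncture (LP) will be performed for participants in non-ELD group". Section 2.8 (Preoperative evaluation) times the suitability evaluation "4 days after ELD to investigate the suitability of potential LPS and then the ELD system will be removed".

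The endpoint is in section 2.9.1: "The primary outcome is the shunting outcomes 1 month after surgery". Failure is "defined as the shunt obstruction, breakage, tubing exposure, malfunction, or infection requiring shunt revision".

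**The concern.** In an open-label trial, blinded assessment is the safeguard that the protocol offers against detection bias in the primary outcome. It works only if those who classify the outcome have not already learned the arm. Here the schedule takes both assessors through a visit at which the arm can be seen, and then asks them to evaluate the same patients after the shunt (LPS), at discharge and at 1 month.

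The risk differs between the components of shunt failure. Breakage and tubing exposure leave little room for opinion. Malfunction, and infection that calls for revision, leave more. A reader of the final report would credit the trial with a protection that its own schedule removes.

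**Working it through.** The claim rests on no figure, so the check is a comparison of sections.

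1. **Who assesses.** Sections 2.2, 2.9 and 2.10 each describe a pair of assessors in the same terms. Section 2.9 gives that pair every time point, including day 4 and 1 month. No separate assessor is named for the 1-month outcome.
2. **What differs between arms on day 4.** ELD patients have a lumbar catheter joined to a drainage system (section 2.7). Controls have a lumbar puncture (LP) only (section 2.2). No sham drain or concealment is described.
3. **Whether the drain is still present.** Section 2.8 puts removal after the day-4 evaluation. On that order a drain shows ELD and its absence shows control, so both arms are revealed.
4. **A conflict to note.** Section 2.7 states that "the drainage period is 3 days and drainage volume is 150 to 200 mL per 24 hours", whereas section 2.8 keeps the system in until the day-4 evaluation is done. These two statements must be reconciled. Which is right is a clinical matter and is not judged here.
5. **Whether step 4 rescues the blinding.** It does not. The scale in section 2.8 and Table 1 is described only for use after ELD, and ELD complications (section 2.9.2) can occur only in patients who had ELD. Anyone who handles either item knows the arm, with or without a visible drain.
6. **Whether someone else could do the day-4 work.** Section 2.5 keeps the intervention clinicians out of all assessment, and no other staff are assigned to it. Section 2.10 mentions a third reviewer, but only for disagreements.
7. **Order of events.** Day 4 comes before the shunt, and the primary outcome is judged 1 month after surgery. The allocation is therefore known before the outcome is evaluated.

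The schedule covers each participant, so the exposure extends to everyone seen on day 4, out of the 100 planned. This counts who is exposed. It does not estimate bias.

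**The case against.** Four arguments can be made on the other side.

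- **The scorer is not named.** Section 2.8 is in the passive and does not say that the two assessors complete the suitability scale. That is true, but sections 2.2 and 2.9 still give them a day-4 evaluation of each participant, and section 2.5 excludes the intervention clinicians. The conflict does not depend on who fills in the scale.
- **The drain may be out.** A reader might infer that it is certainly in place when the assessors arrive. The 3-day period in section 2.7 means that the documents do not settle this. What stands is that the arm is revealed either way.
- **Much of the judgement lies elsewhere.** The endpoint turns in part on whether revision was required, and that decision is made in open-label care. The wording leaves unclear whether the revision clause qualifies every listed event or only the last. This argument stands: perfectly blinded assessors would not remove that source of bias, and the part due to the assessors may be small.
- **An article is condensed.** Covering the drain or using separate staff per visit might be described in a full protocol. But the article itself states the blinding, the assessors, the visit times and the order of drain removal, and these statements conflict with one another.

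**Conclusion.** The point holds as a contradiction. The assessors are declared blind, yet the stated schedule and data-collection duties show them the allocation before they evaluate the primary outcome. Blinding of the analysts is not in question.

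A reader might go further and infer that the result will be shifted in favour of ELD, or try to size the shift by supposing some number of reclassified failures. The documents support neither. They give no misclassification rate, so any such number would be invented, and the direction is as unknown as the size.

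The conclusion assumes that the assessors in sections 2.2, 2.9 and 2.10 are the same pair, as the wording implies, and that the flow chart and schedule table, which could not be read here, do not assign the visits otherwise. The flaw does not by itself invalidate the trial. It is a safeguard on the primary outcome that is claimed but not delivered, and it can be repaired cheaply.

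**What to change.** 1. **Separate the roles within existing staff.** Whoever does the day-4 evaluation in both arms and records ELD complications should not classify the 1-month outcome. For example, one assessor does the day-4 work. The other classifies shunt failure and reads the Evans index from records and scans with ELD and LP entries, arm and date removed. The existing third reviewer settles disputes from the same redacted material.
2. **Do not pass the day-4 suitability score to the intervention clinicians.** Under section 2.8 that score decides who remains in the ELD arm, so the transfer would let the treating team select one side of the comparison. Assign the control arm's day-4 visit explicitly as well.
3. **If the roles cannot be separated,** withdraw the blinding statement for the assessors and keep it for the analysts only.
4. **Reconcile sections 2.7 and 2.8** on how long the drain stays in relative to the day-4 evaluation.
5. **State as a limitation** that the decision to revise a shunt is made in open-label care, so masked classification cannot remove all bias.

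The cost is some redaction work, changes of wording in sections 2.5, 2.9 and 2.10, and reliance on a single primary reader for the masked outcome. No staff are added, and neither the treatment nor the sample size changes.

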### Intervention

2.6

Physicians, neurosurgeons, and clinicians will be trained centrally in advance and reach uniform standard.

### Temporary ELD

2.7

ELD is performed under local infiltration anesthesia and the patients are positioned in the left lateral position. A lumbar catheter is inserted through the L3/4 or L2/3 interlaminar space into the spinal subarachnoid space and then connected to the drainage system. According to previous studies, the drainage period is 3 days and drainage volume is 150 to 200 mL per 24 hours.^[8]^

### Preoperative evaluation

2.8

Repeated evaluation will be performed using the scale, as shown in Table 1, 4 days after ELD to investigate the suitability of potential LPS and then the ELD system will be removed. Patients with scores 4 will be included in this trial and the remaining patients will be excluded. Specifically, the improvement of clinical manifestation is defined as an improvement of 1 point or more in the National Institute of Health stroke scale, Glasgow coma scale, modified Rankin scale, or according to self-assessment.

**Table 1 T1:**

Preoperative evaluation scale after ELD.

### Outcomes

2.9

Two independent and practiced assessors will collect the baseline characteristics and evaluate each participant 4 days after ELD or LP, 1 day after LPS, at the time of discharge and 1 month after LPS. The evaluation schedule is shown in Table 2.

**Table 2 T2:**
[figure not shown]
Study schedule.

#### Primary outcome

2.9.1

The primary outcome is the shunting outcomes 1 month after surgery. Shunting outcomes include shunt failure and shunt success. According to previous studies, which is defined as the shunt obstruction, breakage, tubing exposure, malfunction, or infection requiring shunt revision. Shunt success is defined as the absence of shunt failure.

#### Secondary outcomes

2.9.2

The secondary outcomes include the complications related to ELD, complications related to LPS, and Evens index at each evaluation point.

Meanwhile, considering about the safety of this trial, serious adverse events occurring at any time is recorded.

### Data collection

2.10

Two independent and practiced assessors will collect the data. All data will be recorded in the paper-based Case Record Form and Electronic Data Capture. A third reviewer is required while there are any debates on data collection.

### Data and safety monitoring

2.11

Members of independent data monitoring committee, including 1 physician, 1 statistician, and 1 data analyst, are responsible for monitoring the safety and efficacy of this trial once a month.

### Statistics analysis

2.12

SPSS version 19 (IBM, Armonk, NY) is used to analyze statistics and a *P*-value (2-sided) under .05 is considered to have statistical difference. Kolmogorov–Smirnov test is first used to determine the normality of quantitative data. Quantitative data followed normal-distribution are statistically described as arithmetic mean ± standard deviation. Other quantitative data (non-normal distribution) are statistically described as median (range). Categorical data, such as sex, shunting outcomes, and complications, are statistically descried as number (percent). To compare the 2 groups on quantitative data followed normal-distribution, independent samples *t-*test is used. To compare the 2 groups on the other quantitative data, Wilcoxon rank sum test is used. To compare the 2 groups on categorical data followed normal-distribution, Chi-square test is used.

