#### Inclusion criteria

2.3.1

1.Age >18 years;2.Ventricular expansion occurring secondary to intracranial hemorrhage;3.Evans index >0.3;4.LP indicates that the subarachnoid space of spinal cord is connected with ventricles, and the cerebrospinal fluid opening pressure is between 70 and 200 mm Hg.

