### Sample size

2.4

Previously published reports indicated that the rate of LPS failure for patients with preoperative evaluation using ELD was 15.7%, comparing with a rate of 40.9% for patients without ELD.^[7]^ In this regard, a sample of 45 will be required in this trial with a significance level of 5% (2-sided) and a power of 80% to demonstrate a 20% difference in rate of shunt failure. Considering about the loss to follow-up, the sample size is enlarged to 50 for each group.

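### The Evans index is compared between groups without using the baseline value every patient has, which costs some precision on a secondary outcome

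*Protocol article*

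**What the plan says.** Four parts of the protocol article bear on this point.

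- **Secondary outcomes (2.9.2)** lists "Evens index at each evaluation point". It is the only quantitative outcome named; the primary outcome is shunt success or failure, and the other outcomes are complications and serious adverse events.
- **Inclusion criteria (2.3.1)** requires "Evans index >0.3", so the index is measured before entry in every patient.
- **Outcomes (2.9)** says that the trial's two raters "will collect the baseline characteristics and evaluate each participant 4 days after ELD or LP, 1 day after LPS, at the time of discharge"; a further evaluation follows 1 month after the shunt. That makes four post-baseline points.
- **Statistics analysis (2.12)** applies a Kolmogorov-Smirnov test first. For data judged normal it begins "To compare the 2 groups on quantitative data followed normal-distribution" and names the independent-samples t-test. For the rest, "To compare the 2 groups on the other quantitative data, Wilcoxon rank sum test is used". A P-value "2-sided) under .05 is considered to have statistical difference".

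Section 2.12 mentions no covariate, no change from baseline and no model across visits.

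**The concern.** When an outcome is also measured before randomisation, part of its spread at follow-up is spread that was already there at entry. A two-sample test on follow-up values leaves all of it in the standard error. It also leaves in the estimate whatever difference the groups happened to have at baseline. Adjusting for the baseline value deals with both, and here that value needs no extra measurement.

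The normality check adds a second difficulty. If it is applied at each evaluation, the data decide whether a visit is reported as a difference in means or as a comparison of ranks. Results at successive visits may then not be on the same scale.

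At stake is the width of the interval for one secondary outcome. The primary outcome is binary and is not touched.

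**Working it through.** **The plan's own figures.** The article gives no sample size, standard deviation or correlation for the Evans index. Its only calculation concerns shunt failure: 45 per group "with a significance level of 5% (2-sided) and a power of 80"%, with failure rates given as "using ELD was 15.7%, comparing with a rate of 40.9% for patients without ELD". The unpooled two-proportion formula gives (0.409 × 0.591 + 0.157 × 0.843) × (1.960 + 0.842)² / 0.252² ≈ 46.2, so 47 per group, close to the stated 45. (That text also speaks of a 20% difference, whereas the quoted rates differ by 25.2 points. This is a separate matter, and nothing below depends on it.)

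**Inputs for the Evans index**

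- n = 50 per group (Sample size, 2.4).
- Two-sided 5% level (2.12). The 80% power used below is borrowed from 2.4.
- ρ, the correlation between baseline and follow-up, is not in the documents. Assumed range: 0.3 to 0.8.
- Effects are in units of the follow-up standard deviation (SD), because no SD is given. Baseline and follow-up SD are taken as equal.

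**Formulas**

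- Variance of the group difference, adjusted over unadjusted: 1 − ρ². This ignores the single degree of freedom spent on the covariate, which is negligible with 100 patients.
- Unadjusted sample size per group that matches the adjusted precision: 50 / (1 − ρ²), rounded up.
- Detectable difference at 80% power: (1.960 + 0.842) × √(2/50) = 0.560 SD unadjusted, multiplied by √(1 − ρ²) when adjusted.
- Power for an assumed effect of 0.5 SD: Φ(0.5/0.20 − 1.960) = 0.705 unadjusted. Adjusted, 0.20 becomes 0.20 × √(1 − ρ²).
- Chance baseline difference between groups: its standard deviation is √(2/50) = 0.20 SD. A difference of that size shifts the unadjusted estimate by ρ × 0.20 SD.
- Change from baseline, for comparison: variance ratio 2(1 − ρ).

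**Results, 50 per group**

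| Assumed ρ | Variance ratio, adjusted | Unadjusted n per group to match | Detectable difference (SD) | Power at 0.5 SD | Shift from a 0.20 SD imbalance (SD) | Variance ratio, change score |
|---|---|---|---|---|---|---|
| 0.3 | 0.91 | 55 | 0.535 | 0.746 | 0.06 | 1.40 |
| 0.5 | 0.75 | 67 | 0.485 | 0.823 | 0.10 | 1.00 |
| 0.7 | 0.51 | 99 | 0.400 | 0.938 | 0.14 | 0.60 |
| 0.8 | 0.36 | 139 | 0.336 | 0.986 | 0.16 | 0.40 |

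The gain is small at ρ = 0.3, equivalent to 5 more patients per group. At ρ = 0.7 it roughly doubles the effective sample size. The variance ratio does not depend on n, so it still applies if fewer than 50 per group are analysed. The detectable differences would then be larger.

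**The case against.** The strongest reply is that section 2.12 is a general rule that never mentions the Evans index, and that the article is a condensed account whose analysis plan is not shown. The t-test might be applied to change from baseline, and covariates might be named elsewhere. This stands in part. That follow-up values are compared, visit by visit, is inferred by reading 2.12 together with the secondary outcome as worded in 2.9.2. But 2.12 is not silent: it names the normality test, both group comparisons and the significance level for all quantitative data. The point is therefore about a stated method. A change score would not remove it either: it beats the unadjusted comparison only if ρ exceeds 0.5, and the last column of the table shows a larger variance than covariance adjustment at every ρ considered.

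The second reply is that the size is unknown. This stands. The documents give no correlation, and two of their features could lower it: entry truncates the index at 0.3, and drainage or a shunt comes between baseline and follow-up.

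A reader might draw three stronger conclusions, none of which the documents support.

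- *The planned tests are invalid.* Under randomisation the unadjusted t-test and rank test keep their error rate, and the comparison is unbiased on average. The loss is in precision and in the handling of chance imbalance.
- *Repeated testing without a main visit is an error.* Naming a key visit for a secondary outcome and handling multiplicity among secondary results are commonly left to the analysis plan, and the article makes no confirmatory claim for the Evans index. Values from the same patient would also be correlated, so a false-positive rate that treats the visits as independent tests would be too high.
- *Adjustment makes the groups comparable.* Preoperative evaluation (2.8) excludes patients in the drainage group according to their score after drainage, that is, after randomisation. Baseline adjustment addresses this at most in part, and could put a narrower interval around a selected comparison.

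**Conclusion.** The point holds as a minor matter of efficiency and chance imbalance on a secondary outcome. The stated method leaves out a baseline value that eligibility guarantees for every patient, and it lets a normality test choose between two different comparisons. Over the assumed range of ρ from 0.3 to 0.8, adjustment would remove between 9% and 64% of the variance of the group difference (1 − 0.91 and 1 − 0.36).

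This rests on three assumptions: the range for ρ, a roughly linear relation between baseline and follow-up with similar spread at both, and the reading that 2.12 is applied to follow-up values. The direction is safe: apart from one degree of freedom, adjustment costs essentially no precision even when ρ is low. The amount cannot be settled from the documents.

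**What to change.** Amend section 2.12 for the Evans index as follows.

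- Compare post-baseline values by analysis of covariance with treatment group and baseline Evans index as terms, or by a mixed model over the visits with the same covariate.
- Define baseline as the value obtained before randomisation. The evaluation at 4 days must not serve as baseline, because it follows the allocated procedure.
- Report the adjusted mean difference with its 95% confidence interval.
- Fix the method in advance. Keep the Kolmogorov-Smirnov test, if wanted, for description only, and do not let it choose the analysis.

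The cost is a change of wording. It needs no new patients, visits or measurements, and it runs in the software already named. The primary analysis and the sample size stay as they are. The exclusion after randomisation in section 2.8 needs its own answer, which this change does not supply.
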